### Plans to promote participant retention and complete follow-up {18b}

Patients will get text messages reminding them of the appointment time in advance of the visits. When a patient fails to return on time, a clinical study nurse will contact them through telephone or WeChat. We will streamline the trial procedure to improve the efficiency of treatment.

### Data management {19}

This study uses printed CRF and network-based electronic case report forms for transmission of study information and data. The CRC will fill in the CRF with original data and input them into the electronic data capture (EDC) system. A clinical research assistant will verify the integrity and precision of the data. Only investigators and authorized personnel who know the username and password can get access to the EDC to view the subject’s information. All manual (paper) and electronic data will be kept at the sponsor center for 5 years after publication.

### Confidentiality {27}

Subjects’ name, ID card, telephone, address, and other personal information will be treated anonymously to protect personal privacy. Unauthorized access to clinical trial data will not be permitted except investigators, clinical research center staff, ethics committee members, monitors or auditors. After the trial, clinical trial documents will be uniformly stored in the archive’s office of the institution. Only the members of the original clinical trial research team and inspectors are eligible to view the documents with the approval of the principal investigator (PI) and the director of the clinical research center.

### Plans for collection, laboratory evaluation, and storage of biological specimens for genetic or molecular analysis in this trial/future use {33}

Since biological specimens are not involved in this study, this item is not applicable.

## Statistical methods

### Statistical methods for primary and secondary outcomes {20a}

All data will be analyzed by an independent statistician utilizing SPSS (Version 24.0). The data analysis set in this study will comprise of the full analysis set (FAS), per protocol (PP) set, and safety set (SS). The subjects who receive the treatment at least once after randomization and have corresponding evaluation will be analyzed as the FAS. The subjects who follow the protocol strictly and complete the follow-up will be enrolled in the PP set. SS includes the subjects who have received intervention at least once with safety assessment during the trial. The primary endpoint will be analyzed in the FAS and PP, and secondary endpoints will be analyzed in the FAS. The safety of the treatment will be analyzed in the SS.

Continuous data will be presented as the mean ± standard deviation (SD) or median (P25-P75), while categorical data will be presented as absolute frequencies (percentages). *T* test or Mann-Whitney *U* test will be used to compare primary endpoints between groups. For secondary endpoints, the *t* test or Mann-Whitney *U* test will be used to compare continuous variables between groups, and categorical variables will be analyzed by chi-square test or Fisher’s exact test. The statistical tests used in the study will be two-sided. When *P*<0.05, it will be considered statistically significant.

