**Methods:**

This protocol is designed for a prospective, single-center, assessor-blinded and parallel-group randomized controlled trial. Twenty adult patients aged from 18 to 40 whose orthodontic treatment required bilateral maxillary first premolars extraction will be randomly assigned to the piezocision group and the control group at a ratio of 1:1. The piezocision group will undergo en-masse retraction immediately after the piezo surgery, while the control group will start en-masse retraction directly. Both groups will be followed up every 2 weeks to maintain the retraction force until the end of space closure. The space closing time is set as the primary endpoint. Meanwhile, the secondary endpoints include the change of root length, labial and palatal alveolar bone thickness, vertical bone height, probing depth of maxillary anterior teeth, cephalometric measurements, visual analogue scale, and postoperative satisfaction questionnaire.

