### Outcome measures {12}

Outcome measurements will be recorded before randomization (V0), at the initiation of ER (V1) and after space closure (V2). The primary outcome is the space closing time, which can reflect the effectiveness of piezocision directly. The secondary outcomes are designed to compare the periodontal health, the alveolar bone changes, and torque control of maxillary anterior teeth before and after ER between the two groups. We will also pay attention to the patient-centered outcomes as to evaluate the surgery more comprehensively.

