#### Cephalometric measurements

Preoperative and postoperative lateral radiographs of each subject will be all taken by the same X-ray machine (OC200D, Ingram, Finland). The Dolphin Software (Dolphin Imaging Software V11.7, USA) will be used for cephalometric analysis of the lateral radiographs. Cephalometric parameters are shown in Fig. 4, including SNA, an indicator reflecting the anteroposterior position of the maxillary bone relative to the cranium; MP-SN, the index reflecting the steepness of mandibular body; U1-SN, the index reflecting the inclination of maxillary anterior teeth; and UL-Ep, an indicator of the soft tissue protrusion of the upper lip.

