### Sample size {14}

The sample size will be calculated using PASS system (version 15.0.5) in this study. According to a study reported in 2016, the mean alignment time is reduced by 40% in the intervention group compared to the control group [41]. Our anticipated hypothesis is that the overall treatment time of ER in CG is assumed to be 9 months, while in PG is 5.4 months, with standard deviation of 2 for both groups. Assuming equal variance, 8 participants in each group can provide 90% power to reject the null hypothesis. The significance level is 0.05 and the power is 90%. Considering an anticipated 20% dropout rate, the final sample size is a total of 20, and 10 participants in each group.

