## Data collection and management

### Plans for assessment and collection of outcomes {18a}

After randomization, participants in PG will undergo ER immediately after piezocision surgery, while the ones in CG will receive ER therapy directly. All of them will be asked to fill out the VAS for 7 successive days after ER to compare the discomfort feeling between the two groups. Subjects in PG will additionally fill in the PSQ after the surgery.

The primary outcome is the space closing time (T_V2-V1_), which will be measured from the initiation of ER (V1) till the end of the space closure (V2).CBCT will be taken at V0 and V2 to measure the root length and the thickness of the labial and palatal bone of the 6 maxillary anterior teeth. Dolphin will be used for cephalometric analysis of lateral radiographs to analyze indexes related to dental, skeletal, and soft tissue changes including U1-SN, SNA, MP-SN, and UL-E.

Study staff, including orthodontists, periodontists, clinical study nurses, CRC, assessors, and statisticians, will be trained in data management.

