### Methods for additional analyses (e.g., subgroup analyses) {20b}

No subgroup analyses or any other additional analyses will be planned in this study.

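### Continuous secondary outcomes get unadjusted tests, with change or V2 value left unstated; ANCOVA on the V0 value would settle this and usually gain modest precision

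*Protocol article*

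**What the plan says.** For continuous secondary endpoints, Statistical methods {20a} of the Protocol article provides that a t or Mann-Whitney U "test will be used to compare continuous variables between groups". No covariate is named. Section {20b} closes the list: "No subgroup analyses or any other additional analyses will be planned in this study".

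The form of the endpoint has to be inferred. The abstract says that "the secondary endpoints include the change of root length, labial and palatal alveolar bone thickness, vertical bone height, probing depth of maxillary anterior teeth", which implies change. Outcome measures {12} points the same way, giving as one aim a comparison of "torque control of maxillary anterior teeth before and after ER between the two groups". The list under Secondary outcomes names the measurements themselves, and {20a} does not choose between change and the final value.

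On timing, Outcome measures {12} states: "Outcome measurements will be recorded before randomization (V0), at the initiation of ER (V1) and after space closure (V2"). How firmly a V0 value is established differs by outcome:

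- **Root length, labial and palatal bone thickness:** explicit. Section {18a} says "CBCT will be taken at V0 and V2 to measure the root length and the thickness of the labial and palatal bone", and the Root length section agrees.
- **Vertical bone height:** measured in the same sagittal plane as bone thickness, so presumably from the same scans, but not listed in {18a}.
- **Probing depth:** its section gives no time point.
- **Cephalometrics:** "Preoperative and postoperative lateral radiographs of each subject will be all taken by the same X-ray machine". The early film is not labelled V0.

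Table 1, which may settle the last three, is not shown in the text available.

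**The concern.** With 8 to 10 patients per arm, chance differences at baseline can be sizeable. The baseline mean difference has a standard error of sqrt(2/10) = 0.45 SD at 10 per arm and sqrt(2/8) = 0.50 SD at 8. By the normal approximation, an imbalance above 0.5 SD therefore arises in about 26% and 32% of such trials. Given an imbalance of d, a comparison of V2 values is displaced by r·d and a comparison of changes by -(1-r)·d, where r is the V0-V2 correlation. ANCOVA on V0 removes both in expectation.

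Two things are at stake. One is the width of the intervals for the bone, root and periodontal measures. The other is that two different analyses, with possibly different results, both fit the wording of {20a}.

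**Working it through.** **The plan's own figure.** Sample size {14} assumes 9 against 5.4 months with SD 2 in both groups, a standardised difference of 3.6/2 = 1.8. The exact two-sided t test at 0.05 has power 0.870 with 7 per arm and 0.917 with 8, so 8 is the smallest number reaching 90%. Then 8/0.8 = 10 per arm, 20 in total. The stated size reproduces. It concerns the primary outcome only; the article gives no power or precision figure for a secondary outcome.

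**Inputs.** n = 8 per arm (N = 16, after the planned dropout) and n = 10 per arm (N = 20), from {14}. The correlation r is not in the article and is varied from 0 to 0.95. Further assumptions: equal SD at V0 and V2, approximate normality, and one value per patient and outcome.

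**Formulas.** Variance of the between-group difference, relative to comparing V2 values alone:

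- V2 value: 1, on N-2 df.
- Change from V0: 2(1-r), on N-2 df.
- ANCOVA: (1-r²) × (1 + 1/(N-4)), on N-3 df. The second factor is the price of estimating the slope: 1 + 1/12 = 1.083 at N = 16 and 1 + 1/16 = 1.0625 at N = 20.

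The critical t rises from 2.145 to 2.160 at N = 16 and from 2.101 to 2.110 at N = 20.

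**Example, r = 0.5, N = 20.** ANCOVA variance is 0.75 × 1.0625 = 0.797. Change-score variance is 2 × 0.5 = 1. The ratio of CI widths is sqrt(0.797) × 2.110/2.101 = 0.896, so the interval is about 10% narrower.

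**CI width of ANCOVA as a ratio to each unadjusted t test (8 per arm / 10 per arm):**

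| r (assumed) | against change | against V2 only |
|---|---|---|
| 0 | 0.741 / 0.732 | 1.048 / 1.035 |
| 0.3 | 0.845 / 0.835 | 1.000 / 0.987 |
| 0.5 | 0.908 / 0.896 | 0.908 / 0.896 |
| 0.7 | 0.967 / 0.954 | 0.749 / 0.739 |
| 0.8 | 0.995 / 0.982 | 0.629 / 0.621 |
| 0.9 | 1.022 / 1.009 | 0.457 / 0.451 |
| 0.95 | 1.035 / 1.022 | 0.327 / 0.323 |

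**Check by simulation** (20,000 trials per setting). At 10 per arm and r = 0.5 the simulated ANCOVA variance was 0.792, against 0.797 by formula. Power for a true difference of 1 SD at 10 per arm, in the order V2 only / change / ANCOVA, was 0.56 / 0.56 / 0.66 at r = 0.5, 0.56 / 0.92 / 0.93 at r = 0.8, and 0.56 / 1.00 / 1.00 at r = 0.9.

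**Change or V2.** With V0 as covariate the choice disappears. If V2 = a + b·group + c·V0, then V2 - V0 = a + b·group + (c-1)·V0, and the group effect b is the same.

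**The case against.** The strongest reply is that V0 is probably in use already. The abstract defines these endpoints as changes, so the likely test is a t test on change, and the larger gains against a V2-only test then do not apply. This stands. If r is high, as one might assume for a stable anatomical measure such as root length, the gain over change is close to nil and at r of 0.9 or more becomes a loss of 1-4%.

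A reader might infer that adjustment is free. At this size it is not: it costs one degree of freedom and inflates variance by about 6-8%. The large-sample ratio against change, (1+r)/2, gives 0.95 at r = 0.9; with the small-sample factor it is 0.95 × 1.083 = 1.03 at N = 16 and 0.95 × 1.0625 = 1.01 at N = 20.

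A reader might also infer that the planned tests are biased, or that the trial's safety conclusion hangs on them. The documents support neither. Under randomisation both unadjusted comparisons are unbiased. Section {20a} analyses safety in its own set, separately from the secondary endpoints, and {22} handles harms through adverse event recording.

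Lastly, covariates for secondary outcomes are often left to an analysis plan, and this is a condensed article. That carries some weight, but {20a} does name the tests and {20b} rules out further analyses, so the unadjusted method is stated here rather than left open.

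**Conclusion.** The point holds as a modest gain in precision and clarity on secondary outcomes. It does not correct a bias, and it leaves the primary outcome and the sample size untouched. Against a change-score test, the reading the abstract favours, the ANCOVA interval is about 10% narrower at r = 0.5, 3-5% narrower at 0.7, about equal at 0.8 and 1-4% wider at 0.9-0.95. Against a V2-only test it is about 10%, 25% and 55% narrower at 0.5, 0.7 and 0.9, and up to 5% wider if r is near 0.

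What favours ANCOVA is that r is unknown and probably differs between outcomes. Over r from 0 to 0.95 it loses at most about 5% in width to either alternative. A change score can be about 1.35 times as wide as ANCOVA (1/0.741, at r = 0 and 8 per arm), and a V2-only comparison about 3 times as wide (1/0.327, at r = 0.95).

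These figures rest on the assumed r, equal SDs at V0 and V2, and approximate normality; they describe the t test, not the Mann-Whitney test. They also need a true V0 value, which is explicit only for root length and bone thickness.

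**What to change.** In {20a}, state that each continuous secondary outcome with a V0 value is analysed by ANCOVA, with the V2 value as response and group and V0 as explanatory variables, and that the adjusted group difference is reported with its 95% CI. Specify a rank-based ANCOVA where residuals are clearly non-normal. Confirm for vertical bone height, probing depth and the cephalometric measures that the early measurement is taken at V0, before randomisation. VAS and PSQ keep the planned methods, since VAS starts at V1 and PSQ is completed on the day of surgery, in the piezocision group only.

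The cost is a change of analysis wording, to be made before the data are analysed, plus one degree of freedom per outcome. Where V0 is confirmed, no new measurement is needed, and SPSS, the named software, fits the ANCOVA model.

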### Interim analyses {21b}

No interim analyses will be planned in this study.

### Methods for additional analyses (e.g., subgroup analyses) {20b}

No subgroup analyses or any other additional analyses will be planned in this study.

### Methods in analysis in handle protocol non-adherence and any statistical methods to handle missing data {20c}

For subjects who drop out of the study halfway or have not completed ER at 12 months, the primary outcome will be filled out for 12 months.

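### Giving every dropout a 12-month closing time cuts full-analysis-set power to about 62% at the planned dropout rate, not the stated 90%, and biases the comparison when dropout differs by arm

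*Protocol article*

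**What the plan says.** All references are to the protocol article.

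- **Missing data {20c}.** For patients who "drop out of the study halfway or have not completed ER at 12 months, the primary outcome will be filled out for 12 months". One value therefore covers two situations: leaving early for any reason, and being observed with the space still open at the end of the 12-month observation period set in Trial design {8}.
- **Statistical methods {20a}.** The primary endpoint is analysed in the full analysis set (FAS) and the per-protocol (PP) set. The FAS keeps anyone treated at least once who has an evaluation, so treated dropouts can remain in it. A t or Mann-Whitney "test will be used to compare primary endpoints between groups".
- **Sample size {14}.** The calculation supposes that "the overall treatment time of ER in CG is assumed to be 9 months". Against this it sets a piezocision mean of 5.4 months and uses an SD of 2 in each arm. On that basis "8 participants in each group can provide 90% power to reject the null hypothesis". Then: "Considering an anticipated 20% dropout rate, the final sample size is a total of 20, and 10 participants in each group".
- **Additional analyses {20b}.** None is planned, and no other missing-data method is given for the primary outcome.

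**The concern.** Closing time is a time-to-event outcome with follow-up ending at 12 months. A patient who leaves in month 1 tells us only that closure took longer than the time observed. The rule instead records the slowest result the trial can produce.

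This does two kinds of damage.

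- **Equal dropout.** The filled value lies 12 − 5.4 = 6.6 months above the assumed piezocision mean but only 12 − 9 = 3 months above the control mean. Equal dropout therefore pulls a real difference towards zero and inflates the spread, mostly in the piezocision arm. The sample size section adds 2 patients per arm as if dropouts were absent from the analysis, whereas {20c} puts them back in at 12.
- **Unequal dropout.** The fill turns any imbalance directly into an apparent treatment effect, in either direction. Patients and treating staff are unblinded ({17a}), only one arm has surgery, and {11b} allows withdrawal for adverse events, smoking, pregnancy, medication or any other reason. None of these implies slow closure. With 10 patients per arm, one or two can change the result.

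**Working it through.** **Inputs.** Means 9 and 5.4 months, common SD 2, 20% dropout, 10 randomised per arm (Sample size {14}). "The significance level is 0.05 and the power is 90"%. "The statistical tests used in the study will be two-sided" ({20a}). Fill value 12 months ({20c}).

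**1. The protocol's own figure.** Standardised effect d = 3.6/2 = 1.8. For a two-sample t test the noncentrality is d·√(n/2) on 2n − 2 degrees of freedom.

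- n = 7 per arm: power 87.0%
- n = 8 per arm: power 91.7%

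So 8 is the smallest n per arm that reaches 90%, and 8/0.8 = 10 per arm. The stated sample size reproduces, provided the analysis uses 8 completers per arm.

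**2. The FAS under the fill, by hand.** Let 20% of each arm be set to 12, ignoring for now the cap on completers.

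- Piezocision mean: 0.8 × 5.4 + 0.2 × 12 = 6.72
- Control mean: 0.8 × 9 + 0.2 × 12 = 9.60
- Difference: 2.88 instead of 3.6
- Piezocision variance: 0.8 × 4 + 0.8 × 0.2 × 6.6² = 3.20 + 6.97 = 10.17 (SD 3.19)
- Control variance: 0.8 × 4 + 0.8 × 0.2 × 3² = 3.20 + 1.44 = 4.64 (SD 2.15)
- Pooled SD: √[(10.17 + 4.64)/2] = 2.72 instead of 2

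The standardised effect is 2.88/2.72 = 1.06. The noncentral t formula with n = 10 per arm then gives about 61%. This is only a guide, because the filled data are far from normal.

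**3. The FAS under the fill, by simulation.** 20,000 trials per scenario, 10 per arm, normal closing times, times above 12 set to 12, dropouts set to 12, two-sided 5% tests. The cap lowers the expected difference slightly, to 2.83.

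| Dropouts | Mean difference (months) | t test | Mann-Whitney |
|---|---|---|---|
| *True effect 3.6 months* | | | |
| None, 8 completers per arm | 3.54 | 91.7% | 87.2% |
| 1 per arm | 3.19 | 85.6% | 85.1% |
| 2 per arm | 2.83 | 62.7% | 53.1% |
| Each patient with probability 0.2 | 2.83 | 58.5% | 51.7% |
| 3 piezocision, 1 control | 1.86 | 11.3% | 0.4% |
| 1 piezocision, 3 control | 3.80 | 95.8% | 94.3% |
| 0 piezocision, 4 control | 4.77 | 99.9% | 99.5% |
| *No true effect, both means 9* | | | |
| 2 in one arm, 0 in the other | about 0.6 | about 8% | about 7% |
| 10% against 30% dropout probability | about 0.6 | about 10% | about 10% |
| 4 in one arm, 0 in the other | about 1.2 | 22–23% | 22% |

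Under the null, the t-test and Mann-Whitney columns are false-positive rates and the differences are spurious.

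**4. The alternative.** Log-rank test on a 2-week visit grid, dropouts censored at a visit before their closure, 2 per arm lost, true effect 3.6 months. Separate simulations gave 89–92% power for the asymptotic test, whose size at n = 20 is about 6%, and about 88% for the permutation version. With 3 piezocision and 1 control dropouts the asymptotic test keeps about 89%. With no true effect and 4 dropouts in one arm it rejects in about 6% of trials. All of this assumes that dropout is unrelated to closing time.

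**The case against.** Four points can be made for the protocol.

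- **The PP set keeps the stated power.** The primary endpoint is also analysed in the PP set, where early leavers and their filled values do not appear. With 8 completers per arm that analysis has about 92% power, and the sample size section does not tie its 90% to the FAS. This stands, and it confines the power shortfall to the FAS. But the PP set is not a comparison of the groups as randomised, and it does not repair the FAS result.
- **62% is one scenario.** It needs exactly 2 dropouts per arm, all kept in the FAS. Alignment and levelling follow randomisation and precede retraction ({11a}), so some patients may leave before the closing-time clock starts, and it is unclear whether they would be in the FAS. If one of the two per arm falls outside it, power is about 77%. On the other hand, random 20% dropout gives 56–59%. Two per arm is the dropout the protocol itself anticipates.
- **The 23% false-positive figure is an extreme split.** It is. A 2-to-0 split gives about 8%, and exactly 2 lost in each arm with no true effect gives about 1%, which is conservative. The fill is not conservative in general, though: 4 control dropouts and none in the piezocision arm inflate a true 3.6-month effect to 4.77.
- **Twelve months is reasonable for a patient still open at 12 months.** Agreed. The fault lies in giving early leavers the same value.

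**Conclusion.** The concern holds. The fill rule, the FAS analysis and the sample size calculation do not fit together as written. At the protocol's own 20% dropout, FAS power is about 62% by t test and 53% by Mann-Whitney (56–59% and 49–52% if dropout falls at random), not 90%, and a true 3.6-month benefit is estimated at about 2.8 months. Unequal dropout moves the estimate either way: to 1.86 months with 3 piezocision and 1 control dropouts, and to 4.77 with 4 control dropouts and none in the piezocision arm. It also raises the false-positive rate, to about 8% for a 2-to-0 split and about 23% for 4-to-0.

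These figures rest on normal closing times with the protocol's means and SD, and on treated dropouts staying in the FAS. Fewer dropouts shrink the problem: power is about 86% with 1 per arm. The stated 90% remains right for 8 completers per arm. Because the rule governs the primary endpoint, it needs correcting before the data are analysed.

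**What to change.** Make the primary analysis time-to-event:

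- Kaplan-Meier curves and a two-sided log-rank test in its permutation version, since the asymptotic test is slightly liberal with 20 patients.
- Dropouts censored at their last 2-weekly visit, and patients still open censored at 12 months, with a statement that the 12 months run from the start of retraction (V1).
- The difference in median or restricted mean closing time with a 95% confidence interval.
- The 12-month fill kept only as a labelled sensitivity analysis.
- A statement of how patients who leave before V1 are handled.

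If the fill stays primary, restate FAS power as about 60% at 20% dropout, or recalculate the sample size under that rule.

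The change to time-to-event costs analysis wording only, because visit times and closure status are already recorded every 2 weeks. Its price is the assumption that dropout is unrelated to closing time, which cannot be verified in an open-label trial of 20. The retained fill shows how far the result depends on it. Planned power becomes about 88–90% rather than 92%.
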